#### Power of the original secondary outcomes

As the sample size is based on the primary outcome, we have calculated the power of each of the originally planned secondary outcomes given the sample size of 800 patients.

Death day 91 ± 14 days after randomisation: the implied clinically relevant minimal change in mortality that needs to be detected may be calculated based on (1) the mortality of 17% found in the meta-analysis quoted in the protocol [1]; (2) the assumption that wherever the mRS is dichotomised, the odds ratio for treatment versus control will be the same, the ‘common odds ratio’; and (3) the requirement that this common odds ratio should not be larger than 0.74 (see the sample size calculation). Let the unknown change in mortality in the experimental group be x. If we assume the OR for the dichotomy mRS > 5 compared to mRS ≤ 5 will be 0.74 and the mortality of the control group is 17% as quoted in the meta-analysis, we may find x by solving the equation OR = ((0.17–x)/(0.83 + x))/(0.17/0.83) = 0.74 to obtain x = 0.0384 giving a mortality of 0.1700 – 0.0384 = 0.1316 in the cooled patients versus 0.1700 in the controls. Using a sample size of 800 participants, the power is found to be 0.33.

Death or dependency (mRS > 2) 91 ± 14 days after randomisation: using the same reasoning, the power of this outcome can be calculated by solving the equation (0.63–x)/(0.37 + x))/0.63/0.37 = (0.63 – x)0.63/(0.37 + x)0.37 = 0.74 as 63% of the patients in the meta-analysis had mRS > 2 implying x = 0.0725. The power may then be calculated to be 0.55.

NIHSS score 91 ± 14 days after randomisation: assuming a minimal relevant difference of 2 points, a standard deviation (SD) of 5 points [5], an α of 0.05, and a sample size of 800 participants, the power may then be calculated to 1.00.

EQ-5D-5 L score 91 ± 14 days after randomisation: assuming a minimal relevant difference of 0.05 points, a SD of 0.40 points [6–9], an α of 0.05, and a sample size of 800 participants, the power may then be calculated to 0.42.

WHODAS 2.0 score 91 ± 14 days after randomisation: we originally planned to analyse the World Health Organization Disability Assessment Schedule II (WHODAS 2.0) score at outcome assessment in the period day 91 ± 14 days after randomisation. However, due to difficulties in assessing the clinical meaning, we are not able to calculate the power, and we will thus analyse this as an exploratory outcome.

Brain infarct size 48 ± 24 hours after randomisation: assuming a minimal relevant difference of 2 ml, a SD of 15 ml [10], an α of 0.05, and a sample size of 250 participants, the power may then be calculated to 0.18. Accordingly, this outcome will be exploratory.

Number of patients with at least one serious adverse events 91 ± 14 days after randomisation: assuming a control group event proportion of 20% of patients with at least one SAE, an intervention group event proportion of 10% [11], an α of 0.05, and a sample size of 800 participants, the power may then be calculated to 0.98.

Mean number of SAEs per patients: As we do not have prior data to indicate a probable minimal relevant difference, we cannot calculate power for this outcome. These data will be analysed as an exploratory outcome.

The results of calculations of the power are all shown in Table 2. These results are used to determine the sequence in which the secondary outcomes should be tested using the fixed-sequence approach, i.e. the sequence will be as follows:Score on NIHSS at outcome assessment in the period day 91 ± 14 days after randomisation.Proportion of participants with at least one serious adverse event (SAE) until outcome assessment in the period day 91 ± 14 days after randomisation.Death or dependency, defined as a score on the mRS > 2 at outcome assessment in the period day 91 ± 14 days after randomisation.Brain infarct size at imaging assessment in the period 48 ± 24 hours after randomisation.EQ-5D-5 L score at outcome assessment in the period day 91 ± 14 days after randomisation.Death at outcome assessment in the period day 91 ± 14 days after randomisation.

The exploratory outcomes are:WHODAS 2.0 score at outcome assessment in the period day 91 ± 14 days after randomisation.Number of SAEs per patient until outcome assessment in the period day 91 ± 14 days after randomisation.

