### Statistical analyses

#### Analytical principles

Analyses will be conducted according to the intention-to-treat principle [2] if not otherwise stated.

All primary tests of significance will be two-sided with alpha = 5%. Analyses will be conducted blinded with the two intervention groups coded as, e.g. 0 and 1. Two conclusions will be drawn, one assuming 0 is the intervention group and 1 is the control, and one assuming the opposite. After two abstracts with two conclusions have been written and both accepted by the Steering Group, the code will be broken.

The primary analyses of primary, secondary, and exploratory outcomes will be those of the intention-to-treat population adjusted for the protocol-specified stratification variable and the minimisation variables, and if necessary using data sets generated using multiple imputation.

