### Presentation of results in tables

Tables 3, 4, 5 and 6 show how the results of the analysis of the primary outcome (Table 3), the binary secondary outcomes (Table 4), the continuous secondary outcome and exploratory outcomes (Table 5), and the SAE data (Table 6) will be presented.

**Table 3 Tab3:** Comparison of the distributions of the modified Rankin scale (mRS) between the two intervention groups in each analysis set (intention-to-treat or per protocol)

Population studied	Intervention group	mRS = 0	mRS = 1	mRS = 2	mRS = 3	mRS = 4	mRS = 5	mRS = 6	Common OR	P of difference
		N (%)	N (%)	N (%)	N (%)	N (%)	N (%)	N (%)	(95% CI)	(reference = group 0)
Intention-to-treat (ITT)	Group 0									
	Group 1									
Per protocol (PP)	Group 0									
	Group 1

**Table 4 Tab4:** Comparison of the distributions of the secondary binary outcomes between the two intervention groups in each analysis set (intention-to-treat and per protocol)

Population	Intervention group	Outcomes					
		Death			mRS > 2		
		N (%)	Relative risk (RR) (95% CI)	P	N (%)	RR (95% CI)	P
Intention-to-treat (ITT)	Group 0						
	Group 1						
Per protocol (PP)	Group 0						
	Group 1						

*mRS* modified Rankin score, *CI* confidence interval

**Table 5 Tab5:** Comparison of distributions of the secondary continuous outcomes between the two intervention groups in each analysis set (intention-to-treat or per protocol)

Outcome	Population	Intervention group	Percentiles			N	Mean (SD)	(Minimum, maximum)	*P* of difference
			25%	50%	75%				
NIHSS score Range of possible scores at 91+/-14 days (RS): 0 to 42 Worst = 42	Intention-to-treat (ITT)	Group 0							
		Group 1							
	Per protocol (PP)	Group 0							
		Group 1							
EQ-5D-5 L score at 91+/-14 days RS: 0 to 100 Worst = 0	ITT	Group 0							
		Group 1							
	PP	Group 0							
		Group 1							
Brain infarct size at 48 +/-24 hours Worst = 1	ITT	Group 0							
		Group 1							
	PP	Group 0							
		Group 1							
WHODAS 2.0 score at 91+/-14 days	ITT	Group 0							
		Group 1							
	PP	Group 0							
		Group 1							

*SD* standard deviation, *NIHSS* National Institutes of Health Stroke Score, *EQ-5D-5 L* EuroQoL quality-of-life scale

**Table 6 Tab6:** Amendments made relative to the original statistical analysis plan published in the protocol

Topic described in original statistical analysis plan	Handling of topic in the present amended statistical analysis plan	Reason for action

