#### The secondary and the exploratory outcomes

Frequencies and percentages per group as well as risk ratios with 95% confidence interval (CI) will be reported for binary outcomes. Continuous variables and rate variables will be summarised using mean, standard deviation, 25, 50 and 75 percentiles, and minimum and maximum values.

Logistic regression for binary quantities, the general linear univariate model for continuous outcomes, and the Poisson distribution or negative binomial distribution for rate outcomes will be used. If the assumptions of the Poisson or negative binomial models are not fulfilled with reasonable approximation, a non-parametric method (van Elteren adjusted by nationality of centre) will be used.

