### The interpretation of the effect on outcomes which may only be measured in surviving patients

Formally, three of the original secondary outcomes (NIHSS, EQ-5D-5 L, and infarct size) are only measurable in patients who survive until these outcomes were planned to be measured. This may make the interpretation of a significant effect on each of the last four secondary outcomes somewhat difficult when the power of detecting a small difference between the mortalities in the two groups is low. A surplus of patients in one intervention group relative to the other group may die before the outcome is measured. In the other intervention group, the corresponding surviving patients may (or may not) have very poor outcome values which may make the first group look good if the mortalities do not differ significantly.

Given the sample size of 800 patients and assuming the mortality in one group is 0.17 (e.g. in the control group, see above) the probability of not detecting an absolute reduction in mortality in the experimental group of 0.01, 0.02, 0.03, 0.04, and 0.05 is 0.93, 0.89, 0.81, 0.70, and 0.57, respectively. Thus, differences in mortality of the intervention groups of 5% or less are likely to remain undetected with a relatively high probability. Therefore, we have elected to include the dead patients in the comparison between the two intervention groups by assigning the worst possible score to the dead patients. The EQ5D5L is used to estimate QALYs gained in each arm of the trial population. QALYs are estimated by summing up the time spent in each state multiplied by the quality of life attributed to this state. By definition, the value of QALYs is zero from the time of death onwards. Total QALYs will be computed and reported for each patient for the entire duration of the follow-up.

For the study of prognostic markers in the EuroHYP-1 trial, we will apply similar principles as in the Clarithromycin in Patients with Stable Coronary Heart Disease trial (CLARICOR) trial [18]. The study of prognostic markers will not be part of the primary publication.

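### The NIHSS power of 1.00 rests on an SD of 5 that cannot hold once deaths are scored 42, so the falling-power rule does not put NIHSS first among the secondary outcomes

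*SAP article*

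**What the plan says.** All references are to the SAP article.

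- *Power of the original secondary outcomes* derives the NIHSS power by "assuming a minimal relevant difference of 2 points, a standard deviation (SD) of 5 points", and with "a sample size of 800 participants, the power may then be calculated to 1.00". Table 2 gives a control mean of 8 points and marks the NIHSS inputs as assumed values.
- The same section plans on "the mortality of 17% found in the meta-analysis quoted in the protocol". Applying the common odds ratio of 0.74, it arrives at mortality of "0.1316 in the cooled patients versus 0.1700 in the controls".
- The Discussion states the death rule: "Therefore, we have elected to include the dead patients in the comparison between the two intervention groups by assigning the worst possible score". Table 5 fixes that score for NIHSS: "NIHSS score Range of possible scores at 91+/-14 days (RS): 0 to 42 Worst = 42".
- *The secondary and the exploratory outcomes* assigns "the general linear univariate model for continuous outcomes". The van Elteren fallback in that section is tied to the Poisson and negative binomial models, not to continuous outcomes.
- The Table 2 powers set the order of testing. NIHSS stands first among the secondary outcomes, followed by serious adverse events (0.98), death or dependency (0.55), infarct size (0.47), EQ-5D-5L (0.42) and death (0.33). Under *Multiplicity*, formal testing ends at the first non-significant result, and the remaining P values are exploratory.

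**The concern.** The power calculation and the planned analysis concern two different variables. A mean of 8 with an SD of 5 can describe a score in survivors. It cannot describe a score in which about one patient in six is placed at 42, far from everyone else.

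The figure of 1.00 is the reason NIHSS stands first after the primary outcome. If its real power is lower, a trial can succeed on the primary outcome, miss on NIHSS, and lose the confirmatory status of every later secondary outcome, including serious adverse events, which the plan credits with 0.98.

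**Working it through.** **Inputs.** Difference 2, SD 5, mean 8, N = 800, control mortality 0.17, cooled mortality 0.1316 and death score 42 are all from the SAP article. Alpha is 0.05, two-sided. Equal allocation (400 per arm) is an assumption; it reproduces every power in Table 2.

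**1. The plan's figure.** Power = Φ(d / (SD·√(2/400)) − 1.96). With d = 2 and SD = 5: 2 / (5 × 0.0707) = 5.66, so power is 0.9999. The stated 1.00 reproduces.

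**2. SD of the score actually analysed.** With mortality p, survivor mean m and survivor SD s:

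Var = (1 − p)·s² + p(1 − p)·(42 − m)²

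- If 8 and 5 describe survivors: 0.83 × 25 + 0.17 × 0.83 × 34² = 20.75 + 163.11 = 183.9. The SD is 13.56 and the mean is 0.17 × 42 + 0.83 × 8 = 13.78. The gap between deaths and survivors supplies 163 of the 184 variance units.
- If 8 is the overall mean: the survivor mean is (8 − 7.14)/0.83 = 1.04. Even with no spread among survivors, SD = √(0.17 × 0.83) × (42 − 1.04) = 15.4. With survivor SD 5 it is 16.05.
- For an SD of 5 or less with 17% at 42, the survivor mean would have to be at least 42 − 5/√(0.17 × 0.83) = 28.7.
- The conclusion does not hang on exactly 17%. At 10% mortality, with survivors at 8 (SD 5), Var = 22.5 + 104.0 = 126.5, the SD is 11.2 and power for 2 points is 0.71.

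**3. Power of the linear model, unadjusted.** Where the arms differ in SD, the standard error is √((SD₀² + SD₁²)/400).

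| Case | Difference | SD, control / cooled | Power |
|---|---|---|---|
| 2 points on the analysed score, 8 and 5 for survivors | 2.00 | 13.56 / 13.56 | 0.55 |
| Same, 8 as overall mean, minimum SD | 2.00 | 15.4 / 15.4 | 0.45 |
| Same, 8 as overall mean, survivor SD 5 | 2.00 | 16.05 / 16.05 | 0.42 |
| Survivors gain 2 points, equal mortality | 0.83 × 2 = 1.66 | 13.56 / 14.27 | 0.39 |
| Mortality 17% to 13.16% only | 0.0384 × 34 = 1.31 | 13.56 / 12.40 | 0.30 |
| Survivors gain 2 points and mortality 17% to 13.16% | 13.78 − 10.74 = 3.04 | 13.56 / 13.03 | 0.90 |

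A simulated t-test (4,000 runs, gamma-shaped survivor scores assumed) gave 0.40, 0.29 and 0.90 for the last three rows.

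**4. Covariate adjustment.** The plan adjusts for country and seven minimisation factors. With an assumed R² of 0.2, power is 0.47 to 0.65 without a mortality benefit and 0.95 with survivor gain and mortality benefit together.

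**5. Place in the sequence.** Every value above is below 0.98. At 0.90, NIHSS would be second. At 0.55 it is level with death or dependency. At 0.39 it falls below EQ-5D-5L (0.42).

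**The case against.** The strongest reply is that the plan expects cooling to reduce deaths as well. If 8 and 5 describe survivors, the 2 points most naturally do too, and adding the plan's own mortality figures gives 0.90. This stands. A reader might infer from the lower rows of the table that the test simply has 0.4 to 0.55 power, or that testing would stop at NIHSS in about half of trials with the planned effect. The document does not support either reading. That range holds only without an added mortality benefit; with the plan's own, the NIHSS test misses in about 10% of trials.

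Comparing 0.39 with the 0.55 for death or dependency is also uneven, because the 0.55 is derived under the odds ratio of 0.74 while the 0.39 assumes no mortality effect. Nor is it right that the mean difference is mostly a count of deaths. Deaths dominate the variance, but in the 0.90 case about 1.74 of the 3.04 points (0.8684 × 2) come from survivors.

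Finally, a fixed sequence controls the family-wise error in any pre-specified order, the primary outcome is tested first at full alpha, and later P values are still reported. All true, and it limits the consequence to which secondary outcomes can be claimed. It does not rescue the 1.00.

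**Conclusion.** The 1.00 is correct arithmetic on an input that does not fit the planned analysis; it is not a miscalculation. Under the death rule the SD is about 13.6 to 16. Unadjusted power is about 0.39 to 0.55 for a 2-point difference without an added mortality benefit, about 0.30 for the mortality benefit alone, and about 0.90 with both. No case computed here reaches the 0.98 for serious adverse events, so the plan's ordering rule does not support NIHSS as the first secondary outcome. How far it should move depends on the mortality effect assumed: one place in the favourable case, and to around death or dependency or lower otherwise.

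These figures assume 1:1 allocation, all 800 patients scored, and 17% control mortality. They are marginal powers that ignore the correlation with the primary outcome. The point should be fixed, but it leaves the primary analysis and error control intact.

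**What to change.** Before unblinding:

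1. Recompute the NIHSS row of Table 2 for the score with deaths at 42. State the mortality assumed in each arm, whether the mean, SD and 2-point difference refer to survivors or to all patients, and any R² used.
2. Re-derive the fixed sequence from the corrected powers. If NIHSS is to stay first for clinical reasons, say so and drop the claim that power sets its place.

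The cost is one table row and a revised list; no data collection changes.

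Optionally, pre-specify a rank-based or ordinal test for NIHSS with death as the worst rank, and describe survivors' scores separately. In the simulation above, a rank test had power of 0.997 when survivors gained 2 points with equal mortality, and 1.00 when mortality also fell. The price is lower power if only mortality changes (about 0.16 against about 0.30 for the linear model), and no mean difference in points to report.

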## Methods

### Objective of the EuroHYP-1 trial

The primary aim of the EuroHYP-1 trial is to determine whether systemic cooling to a target temperature of 34–35 °C, started within 6 hours of onset of stroke and maintained for up to 12 hours thereafter, improves outcomes in patients with acute ischaemic stroke. Inclusion and exclusion criteria are described in the design article in Tables 1 and 2 [1].

**Table 1 Tab1:** Baseline characteristics of the participants in the EuroHYP-1 trial

Baseline characteristics	Intention-to-treat population		Per protocol population	
	Intervention group	Control group	Intervention group	Control group
Centre				
- name of centre 1, N (%)				
- name of centre 2, N (%)				
- name of centre 3, N (%)				
- etc				
Intention to perform thrombolysis, N (%)				
Surface cooling, N (%)				
Males, N (%)				
Stroke severity (NIHSS), mean (SD), N				
Age ≤ 65 years, N (%)				
Age, mean (SD), N				
Visible ischaemic lesion on brain imaging, N (%)				
Time since symptom onset, N ≤ 4 hours (%)				

*NIHSS* National Institutes of Health Stroke Score, *SD* standard deviation

**Table 2 Tab2:** Power (based on an α = 0.05) of the secondary outcomes and serious adverse events provided inclusion of 800 patients into the EuroHYP-1 trial

Outcome	Proportion or mean value in control group	Standard deviation in the control group for continuous outcome	Minimal relevant intervention effect - absolute risk reduction relative to control group	Power
Score of NIHSS at 91 +/-14 days (sample size = 800)	8 points^a^	5 points^a^	2 points^a^	1.00
Serious adverse events at 91 +/-14 days (sample size = 800)	20%	NR	10%	0.98
Death or dependency, defined as modified Rankin score > 2 at 91 +/-14 days (sample size = 800)	63%	NR	7.25%	0.55
Brain infarct size at 48 +/-24 hours (sample size = 800)	10 ml^a^	15 ml^a^	2 ml^a^	0.47
EQ-5D-5 L score at 91 +/-14 days (sample size = 800)	0.50 points	0.40 points	0.05 points	0.42
Death at 91 +/-14 days (sample size = 800)	17%	NR	3.84%	0.33

*NIHSS* National Institutes of Health Stroke Score, *EQ-5D-5 L* EuroQoL quality-of-life scale, *NR* not relevant

^a^Assumed values

The null hypothesis is that there is no difference in death and disability as defined by a score on the modified Rankin Score (mRS) scale measured at 91 +/- 14 days after randomisation of the patient.

For an overview of patient schedule and data collection see Fig. 1.

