#### Multiplicity

We cannot claim a significant beneficial effect of the intervention in the trial if the primary outcome is neutral and a secondary outcome is statistically significant. Therefore, any testing addressing the multiplicity problem must not reduce the power of the test of the primary outcome as compared to the situation where we declare the secondary outcomes exploratory and only test the primary outcome using α = 0.05. Consequently, the primary outcome must be tested initially and using α = 0.05. These requirements may be fulfilled if we use a pre-specified testing sequence (fixed-sequence procedure) where each outcome is tested at α = 0.05 [12]. However, as soon as a non-significant result is obtained, the testing is stopped. However, for exploratory purposes we will calculate the *P* values of the remaining tests and present them. We will use the fixed-sequence procedure starting with the primary outcome and followed by the secondary outcomes, and the exploratory outcomes ordered according to descending power (see Table 2).

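### Brain infarct size is both exploratory (N=250, power 0.18) and the fourth confirmatory test (N=800, power 0.47), so the sequence is not fixed for infarct size, EQ-5D-5 L and death

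*SAP article*

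**What the plan says.** The SAP article treats brain infarct size in four places.

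- **Power of the original secondary outcomes, infarct paragraph.** The calculation runs "assuming a minimal relevant difference of 2 ml, a SD of 15 ml", with "a sample size of 250 participants, the power may then be calculated to 0.18. Accordingly, this outcome will be exploratory".
- **Same section, numbered sequence.** The powers set the test order: "These results are used to determine the sequence in which the secondary outcomes should be tested using the fixed-sequence approach". Infarct size stands fourth, after mRS > 2 and directly before EQ-5D-5 L and death: "Brain infarct size at imaging assessment in the period 48 ± 24 hours after randomisation.EQ-5D-5 L score at outcome assessment". The list of exploratory outcomes that follows has two entries, WHODAS 2.0 and the number of SAEs per patient. Infarct size is not one of them.
- **Table 2.** The row reads "Brain infarct size at 48 +/-24 hours (sample size = 800") and gives power 0.47. The infarct paragraph's section says that Table 2 shows all its power results, and opens by saying that the powers are for 800 patients. The 250 is not explained.
- **Multiplicity.** Testing stops at the first non-significant result, and later P values are exploratory. The sequence starts with the primary outcome, "followed by the secondary outcomes, and the exploratory outcomes ordered according to descending power (see Table 2").

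**The concern.** A fixed-sequence procedure protects the family-wise error rate only if there is one order, set in advance. The amendments table (printed as Table 6) gives the purpose as keeping that rate at or below 0.05. Here one section gives infarct size two incompatible roles, each with its own sample size and power. An analyst cannot follow both.

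The outcomes at stake are infarct size itself and the two that follow it, EQ-5D-5 L and death. If infarct size is in fourth place and is not significant, neither of those can be claimed. If it is exploratory or last, EQ-5D-5 L is tested directly after mRS > 2. Someone who knows the results could defend whichever reading allows a claim.

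**Working it through.** **Inputs.** Difference 2 ml and SD 15 ml (infarct paragraph and Table 2). Two-sided test: "All primary tests of significance will be two-sided with alpha = 5"%. N is 250 in the text and 800 in Table 2. The allocation ratio is not stated; I assume 1:1, which reproduces every power in Table 2.

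**1. The plan's two powers.** With N/2 per group, the expected test statistic is 2 / (15 × √(4/N)) = √N / 15, and power ≈ Φ(√N/15 − 1.960).

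- N = 250: 15.81/15 = 1.054; Φ(−0.906) = 0.18. Stated 0.18.
- N = 800: 28.28/15 = 1.886; Φ(−0.074) = 0.47. Stated 0.47.

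Both reproduce. Neither is an arithmetic slip; they answer for different numbers of imaged patients.

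**2. Rank under the plan's own rule.** The other Table 2 powers are NIHSS 1.00, SAE proportion 0.98, mRS > 2 0.55, EQ-5D-5 L 0.42 and death 0.33.

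| Infarct power | Place by falling power |
|---|---|
| 0.47 (N=800) | fourth, between 0.55 and 0.42 |
| 0.18 (N=250) | last, below 0.33 |

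The change points follow from N = [15 × (1.960 + z)]². For power 0.42, z = −0.202 and N = (15 × 1.758)² ≈ 695. For power 0.33, z = −0.440 and N = (15 × 1.520)² ≈ 520. So fourth place needs roughly 695 or more imaged patients, and below roughly 520 the rule puts infarct size last.

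**3. Chance that the later outcomes are tested.** Each figure is conditional on a significant primary outcome and the planned effects. The products assume independent tests and are illustrative only.

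| Version | EQ-5D-5 L tested | Death tested (× 0.42) |
|---|---|---|
| Infarct fourth, N=800 | 1.00 × 0.98 × 0.55 × 0.47 = 0.25 | 0.11 |
| Infarct fourth, N=250 | 1.00 × 0.98 × 0.55 × 0.18 = 0.10 | 0.04 |
| Infarct exploratory or last | 1.00 × 0.98 × 0.55 = 0.54 | 0.23 |

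Positive correlation between outcomes would raise these. In the second row, however, no dependence can lift the unconditional chance of testing EQ-5D-5 L or death above 0.18, because infarct size must be significant first. That test fails with probability 1 − 0.18 = 0.82.

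**4. Error rate if the version is chosen late.** Suppose the earlier tests have passed, infarct size and EQ-5D-5 L are both truly null, and their tests are independent. Under one version the next 5% test is infarct size; under the other it is EQ-5D-5 L. Choosing between them after seeing both gives a false claim with probability 1 − 0.95² = 0.0975, about twice the stated limit.

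**The case against.** **The rest of the plan mostly treats infarct size as confirmatory.** Table 2, the numbered sequence, the exploratory list and the statement that powers are for 800 patients all point that way. The Discussion counts two exploratory outcomes for the main publication, which fits WHODAS 2.0 and SAE counts. Its subsection on outcomes measurable only in survivors still names infarct size among the secondary outcomes. On this view the N=250 sentence may be a remnant, or the protocol, which is not shown, may explain it. This stands as a reason not to assume that exploratory status is the intended one. It does not remove the sentence, which gives its own N, its own power and an explicit conclusion.

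**A reader might infer that EQ-5D-5 L and death are as good as shut out.** The document does not support that without conditions. It needs 250 imaged patients and fourth place together, yet the sentence with 250 also makes the outcome exploratory, and fourth place comes from the 800. At N=800 the power of 0.47 resembles its neighbours (0.55 and 0.42). Nor is infarct size the only narrow step: mRS > 2 stands before it and EQ-5D-5 L before death, so even without it the illustrative figures are only 0.54 and 0.23.

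**A reader might also infer that the error rate is already inflated.** It is not. Each version, fixed in advance, controls it; the harm comes only from choosing after results are known.

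**The Multiplicity wording could allow an exploratory outcome inside the sequence.** That softens the clash of labels, but not the clash over N and rank. The Abstract, the amendments table, the overview of changes and the conclusion all describe the sequence as primary then secondary outcomes only.

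**Conclusion.** The contradiction stands. Infarct size has two sample sizes, two powers, two statuses and, by the plan's own ordering rule, two ranks. Nothing in the SAP article says which governs. As written, the plan cannot be followed for infarct size, EQ-5D-5 L and death. The primary outcome, NIHSS, the SAE proportion and mRS > 2 keep their places and their error control under every reading.

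The size of the consequence depends on a number that the article does not settle, namely how many patients will be imaged. With about 800, the printed order agrees with the rule and only the stray text is wrong. With about 250 and fourth place kept, the 82% failure rate and the 18% ceiling apply, given the planned 2 ml difference, SD 15 ml and 1:1 allocation. The reach probabilities and the 0.0975 also assume independence. Because a confirmatory order is left open, this must be settled before unblinding.

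**What to change.** First state the number of patients expected to have infarct imaging, then fix one status.

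- **If about 800:** delete the N=250, power 0.18 and exploratory wording from the infarct paragraph, and keep Table 2 and the printed order.
- **If about 250:** set the Table 2 row to N=250 and power 0.18. Then either list infarct size as exploratory and outside the sequence, or move it to last, after death.
- **If another number:** recompute the power from that N and place the outcome by the same falling-power rule.

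As a wording correction, remove the exploratory outcomes from the sequence described under Multiplicity. The plan itself says that no power can be calculated for WHODAS 2.0 or SAE counts, so they cannot be ordered by power.

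The cost is SAP wording only, in a dated amendment before the code is broken. Sample size and data collection do not change.
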